### ***Inclusion Criteria***

- Healthy male or female child at least 24 months of age and less than 60 months of age at the time of study entry.
- Resident in the study area and with no plans to travel outside the study area during the period of subject participation.
- Informed consent for the study participation obtained from a parent (or guardian only if neither parent is alive or if guardianship has been legally transferred).
- Willingness and capacity to comply with the study protocol as judged by a member of the clinical trial team.

### ***Exclusion Criteria***

- Serious, active, medical condition, including but not limited to:
  - chronic disease of any body system
  - severe protein-energy malnutrition (weight-for-height Z-score of less than -3)
  - known genetic disorders, such as Down's syndrome or other cytogenetic disorder
- Active wheezing
- History of documented hypersensitivity to eggs or other components of the vaccine (including gelatin, sorbitol, lactalbumin and chicken protein), or with life-threatening reactions to previous influenza vaccinations.
- History of documented hypersensitivity to macrolide antibiotics
- History of Guillain-Barré syndrome.
- Receipt of aspirin therapy or aspirin-containing therapy within the two weeks before planned study vaccination.
- Any suspected or confirmed congenital or acquired state of immune deficiency including but not limited to primary immunodeficiencies including thymus disorders, HIV/AIDS, haematological or lymphoid malignancies.
- Any current immunosuppressive/immunomodulatory treatment or receipt of any such treatment within the six months preceding trial enrolment (for corticosteroids this is defined as a dose of prednisolone (or equivalent) of greater than 2mg/kg/day for one week or 1mg/kg/day for one month. The use of topical corticosteroids is not an exclusion criterion.
- The use of inhaled corticosteroids within the last one month.
- Receipt of an influenza vaccine within the past 12 months.
- Has any condition determined by investigator as likely to interfere with evaluation of the vaccine or be a significant potential health risk to the child or make it unlikely that the child would complete the study?
- Any significant signs or symptoms of an acute illness or infection including:

- an axillary temperature of 38.0°C or above or documented fever of 38°C or above in the preceding 14 days.
- Any acute respiratory infection within 14 days of enrolment visit.

### **Model selection by backwards selection for generalised linear and logistic mixed-effects models**

A multivariable model was first constructed using pneumococcal density (continuous data) as the response variable and including all possible covariates of interest: Group (ref: control vs LAIV), Study timepoint (ref: D0 vs D7 and D21), year of recruitment (ref:2017 vs 2018), presence of asymptomatic respiratory viruses at baseline, age in months, sex, presence of a smoker in the household, type of cooking (re:outdoor open fire vs indoor kitchen). Interactions between group and study timepoint, group and year of recruitment, as well as group and the presence of asymptomatic respiratory viruses were also included.

Backward selection was then undertaken, removing covariates to construct a new model and comparing this reduced model with the previous model using ANOVA-derived P values and Akaike information criteria (AIC). Non-informative covariates were sequentially removed in this way to arrive at the most parsimonious model for our data. Non-significant interaction terms were first removed prior to single covariates. The final model is as stated below:

Pneumococcal density ~ study timepoint + group\*year of recruitment + presence of baseline respiratory viruses + age in months + type of cooking + (1 | participant ID)

A logistic mixed-effects model with pneumococcal carriage (categorical data) as the response variable and including covariates of interest was constructed in a similar way, for each group (LAIV or control) individually. The final model is as stated below:

Presence of pneumococcal carriage ~ study timepoint + presence of baseline respiratory viruses + age in months + type of cooking + (1 | participant ID)

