**Table S2. Factors associated with pneumococcal density during the study period**

| Variable                                             | Change in log10copies/μl | Standard Error | P value # |
|------------------------------------------------------|---------------------------------|----------------|----------------------|
| LAIV receipt at Day 0 (vs control)                   | +0.339                          | 0.129          | 0.0097               |
| Asymptomatic respiratory virus at day 0              | +0.259                          | 0.097          | 0.017                |
| Day 7 ( vs day 0)                                    | +0.153                          | 0.082          | 0.081                |
| Day 21 (vs day 0)                                    | +0.272                          | 0.082          | 0.0015               |
| Recruitment in 2018 (vs 2017)                        | +0.423                          | 0.160          | 0.0091               |
| Age (in months)                                      | -0.015                          | 0.005          | 0.0030               |
| Household cooking indoors (vs outdoors) ^ | -0.275                          | 0.151          | 0.067                |
| Group:year of recruitment interaction                | -0.476                          | 0.195          | 0.016                |

#P values for factors associated with *S. pneumoniae* density are derived from a generalized linear mixed-effect model. Reference levels for each variable are given within brackets. ^Cooking inside (under a roof) compared to cooking using an indoor kitchen. Note 99% of children lived in households where wood/charcoal was primary fuel used to cook regardless of location of cooking.

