**Table S3. Factors associated with pneumococcal density in the control group**

| Variable                          | Change in
log10copies/μl | Standard
Error | P value# |
|------------------------------------------|-------------------------------------|---------------------------|----------------------------|
| Asymptomatic respiratory virus at day 0  | +0.135                              | 0.164                     | 0.41                       |
| Day 7 ( vs day 0)                        | +0.022                              | 0.130                     | 0.86                       |
| Day 21 (vs day 0)                        | +0.232                              | 0.130                     | 0.076                      |
| Recruitment in 2018 (vs 2017)            | +0.402                              | 0.166                     | 0.018                      |
| Age (in months)                          | +0.135                              | 0.164                     | 0.45                       |
| Household cooking indoors (vs outdoors)^ | -0.263                              | 0.277                     | 0.34                       |

#P values for factors associated with *S. pneumoniae* density are derived from a generalized linear mixed-effect model. Reference levels for each variable are given within brackets. ^Cooking inside (under a roof) compared to cooking using an indoor kitchen. Note 99% of children lived in households where wood/charcoal was primary fuel used to cook regardless of location of cooking.

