**Table S4. Factors associated with pneumococcal density in children recruited in 2017**

| Variable                          | Change in
log10copies/μl | Standard
Error | Degrees
of
freedom | P value# |
|------------------------------------------|-------------------------------------|---------------------------|-----------------------------------|----------------------------|
| LAIV receipt at Day 0 (vs control)       | +0.323                              | 0.127                     | 168                               | 0.012                      |
| Asymptomatic respiratory virus at day 0  | +0.140                              | 0.130                     | 168                               | 0.28                       |
| Day 7 (vs day 0)                         | +0.025                              | 0.112                     | 345                               | 0.82                       |
| Day 21 (vs day 0)                        | -0.065                              | 0.112                     | 345                               | 0.56                       |
| Age (in months)                          | -0.014                              | 0.007                     | 169                               | 0.034                      |
| Household cooking indoors (vs outdoors)^ | -0.160                              | 0.246                     | 168                               | 0.52                       |

#P values for factors associated with *S. pneumoniae* density are derived from a generalized linear mixed-effect model. Reference levels for each variable are given within brackets. ^Cooking inside (under a roof) compared to cooking using an indoor kitchen. Note 99% of children lived in households where wood/charcoal was primary fuel used to cook regardless of location of cooking.

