**Table S5. Factors associated with pneumococcal density in children recruited in 2018**

| Variable                                      | Change in
log10copies/μl | Standard
Error | P value # |
|------------------------------------------------------|-------------------------------------|---------------------------|-----------------------------|
| LAIV receipt at Day 0 (vs control)                   | -0.139                              | 0.155                     | 0.37                        |
| Asymptomatic respiratory virus at day 0              | +0.346                              | 0.149                     | 0.022                       |
| Day 7 (vs day 0)                                     | +0.295                              | 0.116                     | 0.012                       |
| Day 21 (vs day 0)                                    | +0.685                              | 0.116                     | <0.0001                     |
| Age (in months)                                      | -0.016                              | 0.008                     | 0.042                       |
| Household cooking indoors (vs outdoors) ^ | -0.359                              | 0.201                     | 0.078                       |

#P values for factors associated with *S. pneumoniae* density are derived from a generalized linear mixed-effect model. Reference levels for each variable are given within brackets. ^Cooking inside (under a roof) compared to cooking using an indoor kitchen. Note 99% of children lived in households where wood/charcoal was primary fuel used to cook regardless of location of cooking.

**Table S6. D7 to D21 change in pneumococcal density in children without asymptomatic respiratory virus at day 0 in the control group**

| Variable                                      | Change in
log10copies/μl | Standard
Error | P value # |
|------------------------------------------------------|-------------------------------------|---------------------------|-----------------------------|
| Day 21 (vs day 7)                                    | +0.311                              | 0.155                     | 0.0501                      |
| Age (in months)                                      | -0.009                              | 0.013                     | 0.48                        |

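### The density model was never offered a year-by-timepoint term, so Table S2's single Day 21 row averages two recruitment years that differ by 0.750 log10

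*Combined protocol and SAP*

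**What the plan says.** The appendix section on model selection starts from main effects for group, timepoint, recruitment year, baseline virus and household and child factors, plus three interactions: "Interactions between group and study timepoint, group and year of recruitment, as well as group and the presence of asymptomatic respiratory viruses". The procedure then only takes terms out: "Backward selection was then undertaken, removing covariates to construct a new model". The final density model is "Pneumococcal density ~ study timepoint + group\*year of recruitment + presence of baseline respiratory viruses + age in months + type of cooking + (1 | participant ID", the last term being a random intercept per child. Timepoint therefore enters once, with the same Day 7 and Day 21 shifts for both recruitment years.

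Table S2 ("Factors associated with pneumococcal density during the study period") reports this model: Day 7 +0.153 (SE 0.082), Day 21 +0.272 (SE 0.082, P = 0.0015), recruitment in 2018 +0.423 (SE 0.160), and group-by-year -0.476 (SE 0.195). Table S4 ("Factors associated with pneumococcal density in children recruited in 2017") and Table S5 ("Factors associated with pneumococcal density in children recruited in 2018") fit each year separately, which lets the day effects differ. Table S3 ("Factors associated with pneumococcal density in the control group") and Table S6, also restricted to controls, combine the years with a main effect of year only. Neither has a by-year counterpart.

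**The concern.** Recruitment year is a design feature: the protocol's section on selection of participants plans two separate January-to-June seasons. If density moved differently over follow-up in the two seasons, a model with one set of day effects reports an average, and nothing in Table S2 says so.

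What is at stake is how the covariate rows are read. On the fold scale, +0.272 is 10^0.272 = 1.87. The protocol's sample-size section for *S. pneumoniae* burden treats 1.5- to 2-fold increases as possibly clinically relevant, so a reader could take the Day 21 row for a rise of that size in the whole cohort. The Recruitment-year row could likewise be taken for a constant difference between the children recruited in the two years.

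**Working it through.** **Inputs** (log10 copies/µl, estimate and SE):

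| Row | Table S2, both years | Table S4, 2017 | Table S5, 2018 |
|---|---|---|---|
| Day 7 vs day 0 | +0.153 (0.082) | +0.025 (0.112) | +0.295 (0.116) |
| Day 21 vs day 0 | +0.272 (0.082) | -0.065 (0.112) | +0.685 (0.116) |
| LAIV vs control | +0.339 (0.129) in 2017 | +0.323 (0.127) | -0.139 (0.155) |

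**1. Reproduce Table S2's day rows as averages.** Tables S10 and S11 give 213 + 108 = 321 children. Table S4's 168 degrees of freedom plus five between-child coefficients suggest about 173 children in 2017, leaving about 148 in 2018 (an inference, since the documents do not print the split).
- Day 21, weighted by children: (173 × -0.065 + 148 × 0.685)/321 = 0.281. Weighted by inverse variance: 0.297 (SE 0.081). Printed: 0.272 (SE 0.082).
- Day 7: 0.149 and 0.155 by the same two weightings. Printed: 0.153.

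The Table S2 day rows are close to weighted means of the two years.

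**2. Compare the years.** They contain different children, so SE = √(0.112² + 0.116²) = 0.161 for either visit.
- Day 21: 0.685 - (-0.065) = 0.750, z = 4.65, P about 3e-6, 95% CI 0.434 to 1.066. As a ratio this is 5.6-fold (2.7 to 11.6).
- Day 7: 0.295 - 0.025 = 0.270, z = 1.67, P = 0.094, 95% CI -0.046 to 0.586.
- Both visits jointly, assuming a correlation of 0.5 between the two estimates because they share day 0: (0.270² - 0.270 × 0.750 + 0.750²)/(0.026 × 0.75) = 22.2 on 2 df, P about 1.5e-5. Day 21 drives this result.

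**3. Set the Table S2 values against the year-specific 95% intervals** (estimate ± 1.96 SE).
- Day 21: 2017 is -0.285 to 0.155 and 2018 is 0.458 to 0.912. The value +0.272 is in neither.
- Day 7: 2017 is -0.195 to 0.245 and 2018 is 0.068 to 0.522. The value +0.153 is in both.

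**4. Recruitment-year row.** With group-by-year in the model, +0.423 is the 2018-minus-2017 difference in controls, averaged over visits. If visits carry equal weight and both arms follow the same time pattern, the day-0 difference is 0.423 - (0 + 0.270 + 0.750)/3 = 0.083. The day-7 and day-21 differences are then 0.353 and 0.833. Treating the year row as independent of the day contrasts and keeping the correlation of 0.5, the SE of the day-0 value is √(0.160² + 0.026/3) = 0.185. Its 95% CI is about -0.28 to +0.45.

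**5. Vaccine rows.** Table S2 implies LAIV effects of +0.339 in 2017 and 0.339 - 0.476 = -0.137 in 2018. The by-year fits give +0.323 and -0.139. In 40 simulated trials with complete visits, adding year-by-timepoint moved the group and group-by-year coefficients by less than 1e-13.

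**The case against.** The strongest reply is that the trial asks about LAIV, so restricting candidate interactions to those with group is defensible, and the omission does not touch the vaccine result. The second half stands. A reader might infer that an ill-fitting time trend distorts the LAIV effect. Step 5 shows that it does not, given near-complete visits.

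A second reply is that Tables S4 and S5 already print the year-specific day effects with standard errors. That also stands for the combined-arm model: the information is there. What is missing is a test of the difference, any sign in Table S2 that its Day 21 row is an average, and any by-year counterpart to Tables S3 and S6.

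Third, a reader might infer that all three rows, Day 7, Day 21 and year, fail to describe either season. That goes too far. Day 7 is compatible with a common effect, and the year row is a contrast between seasons, so it cannot describe one of them.

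Fourth, a reader might conclude that controls in the two years started level and that the year row mostly reflects a later rise. The documents do not establish this. The interval for the implied day-0 difference includes +0.423 itself. The day rows of Tables S4 and S5 also combine both arms, about two thirds of them vaccinated (213 of 321). No year-specific day effect in controls is printed, so these rows are not a clean measure of background drift.

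Finally, the documents contain no statement that density rose generally by day 21. The misreading would come from the table row alone.

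**Conclusion.** The point holds for day 21. Backward selection could not find a year-by-timepoint term because it was not in the starting model, and the appendix's own by-year estimates differ by 0.750 log10 (SE 0.161). The Table S2 row of +0.272 mixes 10^-0.065 = 0.86-fold in 2017, with an interval that includes no change, and 10^0.685 = 4.8-fold in 2018. On the same Wald approximation, adding the term would improve AIC by about 22.2 - 2 × 2 = 18, against (0.476/0.195)² - 2 = 4 for the group-by-year term that was kept.

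Day 7 gives no clear evidence of a year difference. The Recruitment-year row may hide a gap that grows over follow-up, but that rests on a common time pattern in both arms and is imprecise at day 0. The LAIV conclusions are unchanged.

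All of this uses rounded coefficients from two separate fits. The joint test and the AIC figure also use an assumed correlation of 0.5 (the joint statistic runs from 21.7 to 23.6 for correlations of 0.4 to 0.6). The Day 21 comparison needs no such assumption.

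**What to change.** Add year-by-timepoint to the starting density model and to the control-only models behind Tables S3 and S6, refit, and report the interaction test. If the term is retained, replace the single Day 7, Day 21 and Recruitment-year rows with year-specific day effects and the day-0 year difference, and cross-refer to Tables S4 and S5.

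Table S6 should be included because its day 7-to-21 change (+0.311, P = 0.0501) also combines years. Across both arms that change is -0.065 - 0.025 = -0.090 in 2017 and 0.685 - 0.295 = +0.390 in 2018. Table S6 covers only controls without a baseline virus, so these figures show why the check is needed, not what it will find.

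The cost is one refit and no new data: two degrees of freedom, or one in Table S6. Year-specific rows will be less precise, most of all in the control-only models. If controls split about evenly by year, Table S3's Day 21 SE of 0.130 becomes about 0.130 × √2 = 0.18 per year, and about 0.26 for the difference between years. A non-significant test there would therefore not show that the years agree.

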## 20 Study design

### 21 Type of study and design

All primary objectives and most exploratory objectives will be addressed through the conduct of a phase 4, randomized, controlled clinical vaccine trial. A total of 330 healthy children aged 24 – 59 months will be enrolled into one of three groups of equal size (3 x 110 children):

- (i) LAIV-vaccinated (Group A - blood sample at day 0, 2, 21)
- (ii) LAIV-vaccinated (Group B - blood sample at day 0, 7, 21)
- (iii) Control group (Group C)

Allocation concealment will be maintained from the start through the use of sealed envelopes. Block randomization stratified by sex will be used and a randomization sequence will be generated by an MRC Statistician not involved in the study. Investigators will not be blinded to group allocation from this point onwards as the sampling schedule differs between groups. Local laboratory staff will therefore not be blinded for this reason, but samples sent to external laboratories will be blinded (see section 3.2.3).

Two LAIV-vaccinated groups are included in order to achieve several exploratory objectives, which require blood sampling at different time points following vaccination, whilst minimizing the number of times children are bled times (i.e. 2nd blood sample at either day 3 or day 7 post-LAIV, but not both). The unvaccinated subjects will serve as a control group for the primary objective of assessing the impact of LAIV on the nasopharyngeal microbiome. Section 8 details the statistical considerations made to decide on the sample sizes to be recruited. The vaccination and sampling schedules for groups A, B and C are detailed in Tables 1.

Group C subjects will be administered LAIV after the NPS is taken on their day 21 visit, to offer them the same level of protection against influenza illness by participating in the study as those in groups A, B and D.

An additional 35 healthy children aged 24 – 59 months will be recruited in the 2nd phase of recruitment (Jan – June 2018) to assess the objective of how modulation of the nasopharyngeal microbiome with antibiotics impacts the mucosal immunogenicity to LAIV

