## 22 Allocation concealment, randomization and blinding procedures

### 23 Allocation concealment and randomization

Following informed consent, subjects will be assigned a unique subject identification number (section 3.2.2) and details recorded on an enrollment log. If eligibility is confirmed according to the defined inclusion and exclusion criteria (section 5.3), children will be randomized into one of the three equally sized groups as defined in section 3.1 above (for groups A, B and C).

Randomization will be undertaken using pre-prepared, sealed opaque envelopes to maintain allocation concealment. Block randomization stratified by sex will be undertaken using a computer generated randomization sequence pre-prepared by an individual not otherwise involved in the study or its analysis. The block size and randomization sequence will not be known by any member of the investigator team, hence ensuring allocation bias is avoided. Information regarding the group into which a participant has been randomized will be revealed to the team only when opening the envelope.

At the time of randomization, the person undertaking randomization will take the next envelope in numerical sequence. The randomization list will be cross-checked by a second individual both of whom will be required to sign to document the process.

The 35 subjects for group D will be recruited sequentially after recruitment in groups A, B and C have been completed, during the 2nd recruitment season (January – June 2018).

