## **128 Impact of LAIV on the nasopharyngeal microbiome**

Initial sequence data analysis will be performed as described above. Univariate and multivariate linear regression models will be used to study the effect of vaccination with LAIV on microbiota profiles at day 7 and 21 post-vaccination, adjusting for factors such as antibiotic use within the last 1 month, age and nutritional status in all multivariate analyses. Relative effect sizes and their 95% confidence intervals will be calculated for all significant OTUs. Inter-individual variability between vaccinated and unvaccinated children at day 7 and 21 will be calculated using Pearson correlations and tested for significance using the Mann-Whitney U test.

The relative and absolute abundance of the OTUs representing *S. pneumoniae* and *S. aureus* will be compared at day 7 and 21 following vaccination with baseline data and validated via qPCR. Differences in *S. pneumoniae* and *S. aureus* density at day 7 and 21 post-LAIV will be estimated using a regression model, including a fixed effect for the vaccine group and random effects for other relevant factors.

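### Sex, the only stratification factor of the randomisation, should be kept in every LAIV v control model and not left to backward selection

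*Combined protocol and SAP*

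**What the plan says.** **Design.** The Protocol Summary and Sections 21 and 23 agree on how children are allocated. Section 23 states: "Block randomization stratified by sex will be undertaken using a computer generated randomization sequence". No other stratification factor is named. Groups A, B and C are of equal size, so the LAIV v control comparison is 2:1.

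**Appendix, model selection.** Sex is one of the candidate covariates in the starting density model, in a list that includes "presence of asymptomatic respiratory viruses at baseline, age in months, sex, presence of a smoker in the household". Terms are then removed by comparing nested models on P values and AIC. No cut-off is stated and no term is protected. The rule is summed up as "Non-informative covariates were sequentially removed in this way to arrive at the most parsimonious model for our data". After study timepoint and group crossed with year, the final density model ends "year of recruitment + presence of baseline respiratory viruses + age in months + type of cooking + (1 | participant ID". It contains no sex term. Neither do Table S2 (both years), Table S4 (2017) or Table S5 (2018), which are the tables that report a LAIV v control effect on density.

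**Protocol, Section 128.** For microbiota profiles the plan is "adjusting for factors such as antibiotic use within the last 1 month, age and nutritional status in all multivariate analyses". For *S. pneumoniae* and *S. aureus* density it gives a fixed vaccine-group effect and leaves the remaining factors unnamed. Section 129 promises to account for relevant covariates in general terms. None of this names sex or commits to keeping the stratum.

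**The concern.** A stratification factor is part of the design and is known before any outcome is seen. The usual practice is to analyse as randomised and keep it in the group comparison whatever its P value. Here its place in the model was decided by the outcome data.

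Two things are at stake. First, when sex is related to the outcome, a model without it leaves the between-sex variation in the residual although the allocation has already balanced it. The group standard error is then too wide and some precision is lost. Second, the removal cannot be checked, because no coefficient, standard error or P value for sex is shown.

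Parsimony is also a weak reason for leaving sex out of the reported tables. Cooking stays in Table S2 at P = 0.067 and in Table S4 at P = 0.52, and baseline virus stays in Table S4 at P = 0.28. One retained sex term would cost no more than these.

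**Working it through.** **1. Reported figures.**
- Table S2, LAIV term (the 2017 effect, because the model has a group-by-year interaction): 0.339/0.129 = 2.63. P = 0.0086 (normal) or 0.0090 (t with 314 df, assumed). Rounding of the inputs allows up to 0.0094 at that df. The table gives 0.0097 and no df, and a lower df would reach it, so the row is broadly consistent.
- Table S4, LAIV term: 0.323/0.127 = 2.54 on the stated 168 df gives P = 0.0119, against a reported 0.012.

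**2. How much variance sex could explain, given that it was dropped.** Tables S10 and S11 have 213 LAIV and 108 control children, so N is about 321 (assumed close to the density analysis set). A term with statistic t explains about R² = t²/(t² + N), where R² is the share of variance in child-level means.
- Dropped on AIC (one parameter, so t² < 2): R² < 2/(2 + 321) = 0.0062.
- Dropped at P > 0.05 (t² < 1.96² = 3.84): R² < 3.84/(3.84 + 321) = 0.0118.

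**3. Effect on the LAIV standard error.** With sex balanced across groups, adjusting multiplies the SE by about √(1 − R²).
- AIC: √(1 − 0.0062) = 0.997, so 0.129 becomes no lower than 0.1286 (a fall of 0.3%).
- P > 0.05: √(1 − 0.0118) = 0.994, so 0.129 becomes no lower than 0.1282 (a fall of 0.6%).

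With the estimate held at 0.339, the normal P value would go from 0.0086 to no lower than 0.0084 or 0.0082. The degree of freedom spent on sex offsets part of this gain.

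**4. Direction of the error.** For an assumed true sex effect of d standard deviations with equal numbers of each sex, R² = 0.25d²/(1 + 0.25d²), and the actual two-sided error of the test without sex is 2[1 − Φ(1.96/√(1 − R²))]. As a check, 321 children were simulated with 2:1 blocks of six within sex, one outcome per child and 8,000 runs.

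| d | R² | Error without sex, formula | Error without sex, simulated | Error with sex, simulated |
|---|---|---|---|---|
| 0.2 | 0.010 | 0.049 | 0.048 | 0.049 |
| 0.5 | 0.059 | 0.043 | 0.046 | 0.053 |
| 1.0 | 0.200 | 0.028 | 0.026 | 0.048 |

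Leaving sex out makes the test conservative. It does not raise the false-positive rate.

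**5. If the share is taken of the random-intercept variance only, the effect is smaller.** Table S4 has 168 between-child df and five between-child parameters, so about 173 children. The timepoint SE of 0.112 implies a residual variance of 0.112² × 173/2 = 1.09. The LAIV SE of 0.127 with a 2:1 split (115 and 58) gives 0.127²/(1/115 + 1/58) = 0.62 for the variance of child means. The between-child part is 0.62 − 1.09/3 = 0.26, or about 42%. A sex share of 1% of that part then widens the SE by 1/√(1 − 0.0042) − 1, about 0.2%.

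**The case against.** The strongest reply is that sex was not ignored. It stood beside group in the starting model and left only after model comparison found it uninformative. Blocks within sex keep it nearly uncorrelated with group, so removing it can hardly move the LAIV coefficient. The list in Section 128 is illustrative, so not naming sex does not exclude it. All of this stands, and it limits the point to pre-specification and a little precision.

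Three stronger readings are tempting and are not supported.
- A reader might infer that P = 0.0097 and P = 0.012 are doubtful because the model omits the stratum. The error runs the other way: omission is conservative, and a refit should leave these values almost unchanged.
- A reader might suppose that sex explains 2% or 5% of the variance, which would make the SE 1.0% or 2.6% too wide (1/√0.98 and 1/√0.95). For density in the combined model, that conflicts with sex having been removed under the usual cut-offs.
- A reader might extend the point to the carriage model, which also lacks sex. That model is fitted within each group and makes no LAIV v control comparison.

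Two further limits apply. The appendix does not say whether sex was tested separately in the year-specific models, so for Tables S4 and S5 only its absence is documented. And the same selection step removed the group-by-timepoint interaction, which matters more for the meaning of the LAIV term, but that is a separate question.

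**Conclusion.** The point holds as a free improvement of low severity. The only stratification factor was open to removal, was removed by a data-driven rule, and is absent from every table that reports a LAIV effect on density. The protocol does not commit to keeping it, and no sex-adjusted analysis is reported.

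For the combined density model, the SE would fall by about 0.6% or less, from 0.129 to no lower than about 0.128, with little change expected in the estimate. This rests on about 321 children in the analysis, roughly equal numbers of boys and girls, balance on sex surviving into the analysis set, and a cut-off of AIC or P = 0.05. The adjusted estimate itself cannot be computed, because the documents give no sex coefficient and no data by sex. For Tables S4 and S5 the direction is the same, but the bound does not carry over directly. For *S. aureus* and microbiota no fitted model is shown, so the size is unknown.

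**What to change.** In Section 128 and in the appendix, state that sex is a forced fixed effect, outside any backward selection, in every LAIV v control model: microbiota, *S. pneumoniae* and *S. aureus*. Refit Tables S2, S4 and S5 with sex retained and show its coefficient. At minimum, report these refits as a sensitivity analysis beside the present tables.

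The cost is one model term, one degree of freedom per model and a refit. No new data are needed, because sex had to be known to randomise each child.
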